**Fig. 1 Fig1:**
[figure not shown]
Trial Flow Diagram

### Participants’ eligibility

The inclusion criteria for this study are the following: Participants have to be diagnosed with dementia (mild to severe) by a physician and live in institutional care. Participants (if they are able to) or legally authorized representatives (a relative or legal guardian) have to give written informed consent. Participants will be excluded if they have severe hearing problems.

### Recruitment

The study participants will be recruited in cooperation with the participating nursing homes in Thuringia. The nursing homes participating in the study are the following: Sophienhaus Weimar, Friedrich-Zimmer-Haus Weimar, Andreashof Erfurt and Martin-Luther-Haus Erfurt. If necessary to achieve the target sample size, a further nursing home will be recruited.

The nursing homes will send printed information about the study as well as a consent form for telephone contact with a member of the study team to relatives or legal guardians of potential study participants. If possible, a member of the project team will talk to potential participants themselves about the study and obtain their written consent to study participation. When PwD cannot give their consent themselves, the project staff will call relatives or legal guardians. After discussing open questions about the study with the relatives and legal guardians, the consent form will be sent to them with a stamped and addressed envelope.

### Ethical approval

Ethical approval was obtained from the Ethics Committee of the Faculty of Social and Behavioral Sciences of the Friedrich Schiller University Jena (committee’s reference number: FSV 18/06). Written informed consent will be obtained*.*

On the whole, the individualized music intervention represents a non-invasive and low risk intervention. As a possible risk of participating, agitated behavior may temporarily increase in response to the music selected for the individualized playlists. However, project staff or nursing home staff will monitor the participants and intervene if a negative reaction is observed during the music listening sessions. Songs to which participants repeatedly and specifically show negative reactions will be deleted from the playlist and replaced by other songs.

Participation in the study will be voluntary. Participants as well as their relatives or legal guardians can withdraw consent at any time.

### Primary outcome measures

At all four assessment points, quality of life and problem behavior will be assessed via external assessment by the nursing staff using different questionnaires.

#### Quality of life

Single items and visual analogue scales ranging from 0 to 100, based on Wilz and Soellner [29], will be used to assess emotional well-being, sleep quality, and social participation of the PwD. Depressive symptoms will be assessed with the Cornell Scale for Depression in Dementia (CSDD; [30]). The CSDD consists of 19 items and each item is rated on a scale of 0 to 2 (0 = absent, 1 = mild/intermittent, 2 = severe). Cronbach’s *α* is .84.

#### Problem behavior

To assess resistance to care via external assessment, a single item and visual analogue scale, based on Wilz and Soellner [29], will be used. In addition, agitated behavior will be assessed using the German version of the Cohen-Mansfield Agitation Inventory (CMAI; [31, 32]) which measures physically aggressive behaviors (PAB; e.g. hitting), physically non-aggressive behaviors (PNAB; e.g. general restlessness), and verbally agitated behaviors (VAB; e.g. repetitious sentences or questions) over the preceding two weeks. Each of the 29 items is rated on a seven-point scale of frequency. In addition, a five-point scale (from 1 = never to 5 = extremely) will be used for measuring disruptiveness of behavior. Cronbach’s *α* for the German version is .80 [32]. Furthermore, the German version of the Nurses Observation Scale for Geriatric Patients (NOSGER; [33]) will be used. It consists of six dimensions (memory, instrumental activities of daily living (IADL), basic activities of daily living (ADL), mood, social behavior, and disturbing behavior) with five items each. Each item is rated on a five-point scale of frequency of occurrence. The test-retest reliability for the six dimensions lies between .75 and .93.

In addition, goal attainment scaling (GAS; [34]) will be used to evaluate participants’ personal goal attainment. At T1 a member of the nursing staff will specify the participant’s personal goals for the individualized music intervention (IG) or for the standard offer of activities in the nursing home regarding the following six weeks (CG) in assistance by a member of the project team. At T2 nursing staff will rate participants’ personal goal attainment on a five-point scale, where point zero denotes the initial state being maintained or remaining stable. A lower value indicates a mild (− 1) or severe (− 2) deterioration from the certain goal, whereas positive scale values represent a positive change from the initial state in the sense of partial (+ 1) or complete (+ 2) goal attainment (cf. Chew et al. [35]).

During the intervention period, observation of behavior will be conducted three times for 60 min for each participant using an adapted rating scale (based on the Observed Emotion Rating Scale [36] and suggestions from the music&memory working group) with 37 items. The scale is divided into 15 time units of four minutes each. In each time unit it is coded whether the behavior occurs. The aim is to identify emotional and motor changes (facial expression, body movement, and other positive emotional reactions) and activation regarding social participation as well as the occurrence of problem behaviors or other negative reactions.

### Secondary outcome measures

Acceptance and applicability of the intervention will be measured via external assessment by the nursing staff at posttest (T2). For this purpose, a questionnaire (developed by the project team) was used which consists of one visual analogue scale measuring how helpful the music intervention was perceived for the PwD (0 “not helpful at all” to 100 “extremely helpful”) and the following five single items. The nursing staff will be asked to evaluate the frequency (too much, just right, too little) and duration (too long, just right, too short) of the music intervention as well as their satisfaction with the implementation (idea of an individualized music intervention and type of music: very dissatisfied, slightly dissatisfied, largely satisfied, or very satisfied), and whether they thought that the music sessions should be continued for each participant.

### Procedure

Six weeks before the intervention starts (T0), the severity of dementia will be assessed with the Mini-Mental State Examination (MMSE, [37]). At the same time, the nursing staff will conduct the first external assessments by completing different questionnaires regarding quality of life and problem behavior of PwD as described above. If the respective nursing staff member conducting the external assessment is uncertain about his or her assessment, a member of the project staff will attend the case conferences in the nursing home to obtain the missing information.

At T0, additionally relevant personal data of the participating PwD (e.g. medication, other physical and psychological diagnoses) will be assessed. As part of the assessments at T1, T2, and T3, any changes in personal data will be recorded. After completion of T0, participants will be randomly assigned to IG and CG.

Following randomization, the individualized playlists of the preferred music will be created for participants of the IG. We will gather information from family members, nursing home staff, and directly from participants if they are able to verbalize their personal preferences. A questionnaire developed by the project team (based on Gerdner [38], Gerdner and Schoenfelder [39], and a search of popular music from different decades) including a list of examples of popular artists and song titles will be used to identify personally-relevant music for each participant. Additionally, a telephone or face-to-face interview will be arranged with family members and/or participants themselves to get more detailed information about their music preferences. Based on this information, up to three individualized playlists for each participant will be compiled. Standardized documentation sheets will be used to record the characteristics of each playlist (number of playlist, number of tracks, duration of compilation).

Further external assessments by the nursing staff regarding quality of life and problem behavior will be conducted directly before (T1) and after the intervention (T2). At posttest, acceptance and applicability of the music intervention will be assessed. The follow-up assessment will take place six weeks after the end of the intervention (T3).

During the intervention period, the observations of behaviors will be conducted for IG and CG. To ensure a high methodological quality for the observations of behaviors, the project staff will be thoroughly trained in using the rating scale. At the beginning of the first intervention period, Cohen’s Kappa and percent agreement will be calculated to determine intercoder reliability. For this purpose, every observation of behavior will be conducted by two members of the project staff during the first two weeks. In case of an insufficient reliability, a training for improving intercoder agreement will be conducted.

Data will be collected on paper forms and data entry will be performed at the coordinating center in Jena by research assistants who are experienced in data entry. Double data entry will be performed for a random subset of data. All study-related information will be stored securely at the coordinating center.

### Intervention

Participants of the IG will listen to their individualized playlists on MP3 Players and headphones for 20 min every other day over the course of six weeks for a total of 21 music sessions. During the music intervention period, the project staff or nursing home staff will accompany and monitor the participants. As no comparable control intervention is available, the CG will receive standard care. Participants of both groups can use all simultaneous offers in the nursing home. If additional music therapy activities take place, they will be systematically documented. During the six weeks of intervention, observation of behavior will be conducted for the IG and the CG every other week for 60 min (three observations per participant). In the IG, participants’ behavior will be observed for 20 min before the music listening session starts, during the 20-min listening session, and for 20 min after the end of the music listening session.

For all music listening sessions, date, time, and duration of the session as well as, if necessary, the reason why a session had to be cancelled will be recorded by project staff or staff from the nursing home using a standardized documentation sheet. The suitability of the playlists will be checked and documented during the music listening sessions and playlists will be continuously adapted over the intervention period as needed.

### Sample size

Based on findings from a meta-analysis [27], small effect sizes on quality of life and problem behavior of PwD are expected (*f* = 0.2).

Hypothesizing this small effect size in a two-group design, an *α* of .05 and a power (1 − β) of 0.95, a sample of *n* = 92 participants is needed. Assuming a dropout rate of 27% (18% [40] and 36% [21]), 130 PwD will be recruited.

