## Methods

### Design

This study is a multi-center RCT with a baseline (T0; six weeks before treatment), pretest (T1), posttest (T2), and follow-up (T3; six weeks after treatment) design. The study will take place successively in four to five nursing homes in Thuringia, Germany. The participants will be randomly assigned to an intervention or a control group. Following T0, random allocation in a 1:1 ratio will be performed stratified by gender using a computer-generated randomization list for each nursing home. The randomization will be performed by a member of the study team not involved in the baseline assessment using the random number generator Random.org.

At four assessment points, the nursing staff will conduct external assessments (see trial flow diagram, Fig. 1). Additionally, the participants’ behavior will be observed during the intervention period.

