### Data analysis

The data will be analyzed using SPSS (IBM Corp., Armonk, NY) and R (R Development Core Team, Vienna, Austria).

Descriptive statistics of playlist characteristics, number of music sessions, music session duration, the proportion of cancelled sessions, and why sessions were cancelled will be reported as indicators of implementation quality.

To check whether the randomization was successful, baseline characteristics and the pre-test levels of the outcome measures will be compared between IG and CG. Further analyses will be adjusted for any potential significant differences.

“As randomized” analyses will be performed retaining participants in the group to which they were originally allocated regardless of protocol adherence. In addition, per protocol analyses will be conducted based on the sample of participants who adequately adhered to the intervention protocol by completing at least five out of the 21 music listening sessions. Any differences between protocol non-adherers and protocol adherers as well as dropouts and those who complete the study will be analyzed regarding baseline characteristics and pre-test levels of the outcome measures.

Multilevel models for discontinuous change [41] will be performed for the primary outcomes to evaluate whether outcomes show different change patterns between IG and CG from baseline (T0) to pretest (T1) to posttest (T2) to follow-up (T3). Following Göllner et al. [42], three contrast variables will be computed by subtracting the baseline values from pretest (T1-T0), posttest (T2-T0) and follow-up values (T3-T0), respectively. The multilevel models will have two levels: the four assessments of the outcome variables as level-1 and participants as level-2. To examine average treatment effects, group membership will be included in the multilevel models as a dichotomous level-2 predictor (0 = CG, 1 = IG). Differential effectiveness will be analyzed by including the severity of dementia and its interaction term with the group membership variable as person-level moderator variables. Full maximum likelihood estimation will be used to account for missing data.

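### The printed sample-size inputs do not give n = 92, and 95% power for a small effect holds only under a correlation or effect scale that the protocol does not state

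*Protocol article*

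**What the plan says.** The Sample size section of the protocol article says that, on the strength of a meta-analysis, "small effect sizes on quality of life and problem behavior of PwD are expected (*f* = 0.2"). It continues "Hypothesizing this small effect size in a two-group design", with alpha .05 and "a power (1 − β) of 0.95, a sample of *n* = 92 participants is needed". It then adds: "Assuming a dropout rate of 27% (18% [40] and 36% [21]), 130 PwD will be recruited". It gives no number of measurements, correlation between assessments, sphericity value or named test.

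The Design section fixes the allocation: "random allocation in a 1:1 ratio will be performed stratified by gender". The Data analysis section plans a multilevel model with "the four assessments of the outcome variables as level-1 and participants as level-2", in which "three contrast variables will be computed by subtracting the baseline values from pretest (T1-T0), posttest (T2-T0) and follow-up values (T3-T0), respectively". Group enters as a two-valued participant-level predictor. None of the three contrasts is singled out as the one the trial is powered for.

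**The concern.** The sentence offers 92 as the consequence of a listed set of inputs. For a two-group comparison those inputs form a complete set, and the answer they give is more than three times as large (328/92 = 3.6). If a different formula was used, the value f = 0.2 may no longer carry the meaning that the text gives it.

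The Background and Discussion present the large sample as the remedy for earlier small trials. A null result would be read against 95% power for a small effect, and so as good evidence that no small effect exists. If the 95% belongs to a much larger effect, that reading would be wrong.

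**Working it through.** **Inputs.** f = 0.2, alpha .05 (taken as two-sided), power 0.95, n = 92, 27% dropout and 130 recruited, all from Sample size; 1:1 allocation from Design; four assessments and the T2-T0 contrast from Data analysis. For two equal groups d = 2f = 0.4. The correlation r between assessments is not given, so every value of r below is an assumption.

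**Step 1: the printed inputs.** Two-group F test with 1 and N − 2 degrees of freedom and noncentrality λ = N·f².

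- N = 92: λ = 92 × 0.04 = 3.68, power 47.5%.
- N = 130: λ = 5.20, power 61.9%.
- N = 328: λ = 13.12, power 95.1%. This is the required size; N = 326 falls just short.
- A one-sided test would need about 272.

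The stated 92 is not reproduced.

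**Step 2: can 92 be reached another way?** Within-between interaction of a repeated-measures ANOVA with m measurements and sphericity value ε: λ = f²·N·m·ε/(1 − r), with (m − 1)ε and (N − 2)(m − 1)ε degrees of freedom.

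| m | r | ε | λ at N = 92 | Power at 92 |
|---|---|---|---|---|
| 2 | 0.45 | 1 | 0.04 × 92 × 2/0.55 = 13.38 | 95.1% |
| 3 | 0.30 | 1 | 0.04 × 92 × 3/0.70 = 15.77 | 95.1% |
| 4 | 0.50 | 0.5 | 0.04 × 92 × 4 × 0.5/0.50 = 14.72 | 95.1% |

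All three return 92 exactly, so the calculation that was run cannot be identified. Neighbouring inputs give other sizes: m = 2, r = 0.5 needs 84, and m = 4, r = 0.5, ε = 1 needs 56.

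**Step 3: what f = 0.2 means in that formula.** Let the arms differ by δ (in SD units of a single assessment) at the assessments where the effect is present. The interaction f is then (δ/2) × s, where s is the standard deviation over the m assessments of a 0/1 indicator of presence. Hence δ = 0.4/s.

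- m = 2: s = 0.500, δ = 0.80.
- m = 3, effect at one or two assessments: s = 0.471, δ = 0.85.
- m = 4, effect at T2 and T3: s = 0.500, δ = 0.80.
- m = 4, effect at T2 only: s = 0.433, δ = 0.92.

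Each is at least twice the 0.4 SD that f = 0.2 denotes for two groups.

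**Step 4: power of a planned contrast for 0.4 SD at N = 92.** The change T2-T0 has variance 2(1 − r) in units of the single-assessment variance, so f becomes 0.2/√(2(1 − r)). For T2 adjusted for T0, f becomes 0.2/√(1 − r²). The F test of Step 1 then gives:

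| Assumed r | T2-T0 change: f | Power | T2 adjusted for T0: f | Power |
|---|---|---|---|---|
| 0.3 | 0.169 | 36% | 0.210 | 51% |
| 0.5 | 0.200 | 48% | 0.231 | 59% |
| 0.7 | 0.258 | 69% | 0.280 | 76% |
| 0.8 | 0.316 | 85% | 0.333 | 89% |

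The change contrast reaches 95% near r = 0.86, and the baseline-adjusted comparison near r = 0.85.

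**Step 5: dropout.** 92/(1 − 0.27) = 126.03, so 127; 130 × 0.73 = 94.9. The recruitment figure of 130 is consistent with 92 completers.

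**The case against.** The best defence is that the planned analysis is not a single comparison of two groups. Outcomes are measured four times and modelled over time, and the reference to two groups may describe only the number of arms. One of the matches in Step 2 uses the trial's own four assessments. A journal article may leave the correlation and sphericity value to a fuller document, and their absence alone is not the complaint.

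Much of this stands. A reader might infer from Step 1 that the trial needs 328 participants, that its power is about 48%, or that it is close to a coin toss for a small effect. The document does not support these as properties of the planned analysis, because they apply to one measurement per person. T2-T0 is also only one of three listed contrasts, chosen here because it spans the intervention, and the correlations are illustrative. Other summaries do better: with 92 participants, equal correlations and a 0.4 SD difference, the mean of T2 and T3 adjusted for the mean of T0 and T1 has 84% power at r = 0.5 and 95% at r = 0.7. That is not, however, a contrast the plan describes. Nor can one infer that the sponsor miscalculated; a correct run of a repeated-measures formula may lie behind the 92.

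The defence does not rescue the sentence as printed. If f = 0.2 is the two-group effect, 92 does not follow without a high correlation. If it is an interaction f, 92 may follow, but the effect is then about 0.8 to 0.9 SD and the description as small fails.

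**Conclusion.** The point holds as a statement that is wrong as written: the size and power do not follow from the inputs given for them. From those inputs N is 328, and 92 gives 47.5% for a single two-group comparison. Under the interaction formulas that return 92, the 95% refers to a difference about twice 0.4 SD. For a 0.4 SD difference on the planned T2-T0 contrast, 92 participants give 36% to 85% power over correlations of 0.3 to 0.8, with 95% only near 0.86.

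These figures assume 92 analysed participants in equal arms, a two-sided test, equal variances at each assessment and, for Step 4, a T0-T2 correlation that the protocol does not give. The trial's actual power cannot be settled from the document. What can be said is that 95% power for a small effect is not supported by what is stated.

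**What to change.** Keep 130 recruited and restate the Sample size paragraph:

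- name the contrast and test for which the trial is powered, and the number of measurements used;
- give the assumed correlation between assessments and the sphericity value, with their basis;
- express the assumed effect as a between-arm difference in SD units, so that the meaning of f = 0.2 is plain;
- show power at 92 completers over a range of correlations, labelled as assumptions, in the manner of Step 4;
- withdraw the claim of 95% power for a small effect unless the stated correlation supports it.

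The cost is one reworded paragraph, with no extra participants and no change to design or analysis. The downside is that the stated power will probably look less favourable, and a null result will have to be read with that in mind.

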### Monitoring

A data monitoring committee will not be necessary, as the clinical trial does not involve a high-risk intervention. We do not expect adverse events or other unintended effects of the intervention. During the entire study period, participants will be accompanied by the project staff and nursing home staff.

### Data analysis

The data will be analyzed using SPSS (IBM Corp., Armonk, NY) and R (R Development Core Team, Vienna, Austria).

Descriptive statistics of playlist characteristics, number of music sessions, music session duration, the proportion of cancelled sessions, and why sessions were cancelled will be reported as indicators of implementation quality.

To check whether the randomization was successful, baseline characteristics and the pre-test levels of the outcome measures will be compared between IG and CG. Further analyses will be adjusted for any potential significant differences.

“As randomized” analyses will be performed retaining participants in the group to which they were originally allocated regardless of protocol adherence. In addition, per protocol analyses will be conducted based on the sample of participants who adequately adhered to the intervention protocol by completing at least five out of the 21 music listening sessions. Any differences between protocol non-adherers and protocol adherers as well as dropouts and those who complete the study will be analyzed regarding baseline characteristics and pre-test levels of the outcome measures.

Multilevel models for discontinuous change [41] will be performed for the primary outcomes to evaluate whether outcomes show different change patterns between IG and CG from baseline (T0) to pretest (T1) to posttest (T2) to follow-up (T3). Following Göllner et al. [42], three contrast variables will be computed by subtracting the baseline values from pretest (T1-T0), posttest (T2-T0) and follow-up values (T3-T0), respectively. The multilevel models will have two levels: the four assessments of the outcome variables as level-1 and participants as level-2. To examine average treatment effects, group membership will be included in the multilevel models as a dichotomous level-2 predictor (0 = CG, 1 = IG). Differential effectiveness will be analyzed by including the severity of dementia and its interaction term with the group membership variable as person-level moderator variables. Full maximum likelihood estimation will be used to account for missing data.

Average personal goal attainment according to the GAS-ratings of the nursing staff will be calculated by first calculating the average personal goal attainment for each participant across all of his/her specified goals, and then calculating the average goal attainment across all participants separately for IG and CG. In addition, the proportion of participants who completely or partially attained their goals, experienced at best no change with regard to their personal goals, and the proportion who reported mild or severe deterioration on the specified goals separately for IG and CG will also be calculated. Frequency scores will be compared between the two groups.

For analyzing the behavioral observation data, frequency scores will be computed for time units 1–5 (i.e. the first 20 min of behavior observation; pre-intervention period in the IG), 6–10 (i.e. the second 20-min period; intervention period in the IG) and 11–15 (i.e. the third 20-min period; post-intervention period in the IG) by summing up how often each behavior occurred in each of the three observation periods. Frequency scores for each period will subsequently be compared both within and between intervention groups in order to identify significant changes in frequencies of behaviors.

Frequencies and percentages in each response category will be computed for the secondary outcome measures as indicators of the acceptance and applicability of the intervention.

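### Adjustment covariates are picked by significance tests that include the T1 scores, which are taken after randomisation and are themselves a modelled response

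*Protocol article*

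**What the plan says.** The rule is in the Data analysis section of the protocol article: "To check whether the randomization was successful, baseline characteristics and the pre-test levels of the outcome measures will be compared between IG and CG". The next sentence gives the consequence: "Further analyses will be adjusted for any potential significant differences". No significance level is attached to it; the only alpha in the article is the .05 under Sample size.

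The timing is fixed elsewhere. The Design section defines a "baseline (T0; six weeks before treatment), pretest (T1), posttest (T2), and follow-up (T3; six weeks after treatment) design", so the pretest is T1 and not a loose name for baseline. It then places allocation: "Following T0, random allocation in a 1:1 ratio will be performed stratified by gender". The Procedure section agrees and adds a step that concerns one arm only: "Following randomization, the individualized playlists of the preferred music will be created for participants of the IG". Nursing staff supply the T1 ratings shortly before the first music session.

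The Data analysis section also makes T1 a response. The four assessments form level 1 of the multilevel model, and T1-T0 is one of three contrasts, beside T2-T0 and T3-T0. Dementia severity enters only as a moderator.

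**The concern.** The rule has three weaknesses.

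- **T1 cannot check randomisation.** It is measured after allocation. By then nursing home staff have been a source of information for the intervention arm's playlists (Procedure), and at T1 a member of the nursing staff sets goals that are worded by arm (Problem behavior). The Discussion says that blinding is not possible. A T1 difference may be chance or may reflect knowledge of the arm; it is not evidence about the allocation process.
- **T1 would stand on both sides of the model.** If T1 differs because of something that happened after allocation, adjusting for it removes part of the difference that the T1-T0 contrast exists to show. That contrast could reveal rating influenced by knowledge of the arm before any music is played.
- **Significance is the wrong criterion for true baseline variables.** Under correct randomisation each has the same 5% chance of being flagged, whether or not it predicts the outcome.

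At stake are the interpretability of T1-T0, a possible distortion of other estimates if T1 is used as a covariate, and an adjustment set decided by chance.

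**Working it through.** The plan gives no figure for this rule, so there is none to reproduce. The inputs are N = 92, hence 46 per arm, and f = 0.2, hence d = 2 × 0.2 = 0.4 for two equal groups (Sample size). Assumptions, because the document gives no values: test level .05, SD 1, correlation between assessments 0.3 to 0.7, and a post-allocation T1 shift of 0, 0.2 or 0.4 SD.

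**1. Chance triggering.** The outcome sections list four single-item or visual analogue measures, the CSDD, three CMAI subscales and six NOSGER dimensions: 4 + 1 + 3 + 6 = 14 scores at T1. How they will be scored is open, so take 12 to 15. With independent scores, P(at least one p < .05) = 1 − 0.95^k:
- k = 12: 46%
- k = 14: 51%
- k = 15: 54%

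Positive correlation between scores lowers these.

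**2. Adjusting for T1 when T1 has shifted.** Let the true T1 shift be 0.4, with no difference at T0 and correlation ρ = 0.5.

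- The within-arm slope of T1-T0 on T1 is 1 − ρ = 0.5. The T1-adjusted group difference is 0.4 − 0.5 × 0.4 = 0.20.
- The standard error of the T1 difference is √(2/46) = 0.2085 and the critical value is 1.987, so T1 is flagged when the observed difference exceeds 0.414. This happens in about 47% of trials.
- In the unflagged 53%, the mean observed T1 difference is about 0.243 (a normal with mean 0.4 and SD 0.2085, truncated at 0.414). The unadjusted contrast there averages 0.5 × 0.243 + 0.20 = 0.32.
- Average under the rule: 0.527 × 0.321 + 0.473 × 0.20 = 0.26, against a true 0.40.

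Simulation (46 per arm) agrees at 0.26 and gives 0.21 and 0.32 at ρ = 0.3 and 0.7. With a shift of 0.2 and ρ = 0.5, the contrast goes from 0.20 to 0.16. With no shift its mean stays at zero.

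**3. The other estimates, with a T1 shift of 0.4 and a true effect of 0.40.**
- T2-T0: the slope on T1 is ρ − ρ = 0 under compound symmetry and under equally spaced AR(1). There is no bias; power falls by about 1 to 2 points.
- T3-T0: unbiased under compound symmetry. Under AR(1) with ρ = 0.5 the slope is ρ² − ρ = −0.25, so the adjusted value is 0.40 + 0.25 × 0.4 = 0.50, and 0.47 on average under the rule.
- T2 adjusted for T0: at ρ = 0.5 it falls to 0.32 (compound symmetry) or 0.27 (AR(1)) under the rule. Over ρ from 0.3 to 0.7 the range is 0.24 to 0.34.

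**4. True baseline covariates.** In a model with one post score and no T0 score, power without adjustment and under the rule is 47.3% and 47.4% (covariate-outcome correlation r = 0.3), 47.3% and 47.7% (r = 0.5), and 47.5% and 48.4% (r = 0.7). The rule gains at most about 1 point. Type I error under the rule is 4.7%, 4.3% and 3.6%.

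With T0 in the analysis, as this plan has it, and a covariate assumed equally correlated with T0 and T2, power for the rule against always adjusting is:

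| Analysis | T0-T2 correlation | r | Rule | Always adjusted |
|---|---|---|---|---|
| T2-T0 | 0.5 | 0.3 | 46.8% | 46.5% |
| T2-T0 | 0.5 | 0.5 | 46.6% | 46.3% |
| T2-T0 | 0.7 | 0.7 | 68.7% | 68.8% |
| T2 given T0 | 0.5 | 0.3 | 57.3% | 58.0% |
| T2 given T0 | 0.5 | 0.5 | 58.4% | 63.4% |
| T2 given T0 | 0.5 | 0.7 | 60.3% | 75.0% |
| T2 given T0 | 0.7 | 0.3 | 74.3% | 74.9% |
| T2 given T0 | 0.7 | 0.5 | 75.6% | 77.4% |
| T2 given T0 | 0.7 | 0.7 | 76.9% | 83.0% |

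The absence of gain for T2-T0 follows from the equal-correlation assumption: such a covariate does not predict change.

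**The case against.** The strongest defence is that T1 precedes the first session, so its expected difference between arms is zero unless knowledge of the arm or the playlist work moves it. The document gives no size for such a shift. T2-T0, which ends at the close of treatment, is unaffected on average in the settings checked. The article also does not say how a covariate would enter: as a main effect only, with complete data, T1 would leave the group-by-time contrasts unchanged. The distortions computed above arise when the covariate acts on the contrast itself. All of this stands and limits the size of the harm.

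It is also fair that a fixed covariate list is commonly left to the analysis plan. Its absence from the article is not the point; the point is the rule that the article does state.

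A reader might infer more than the document supports:
- **That the rule costs much power.** In a single-post-score model with no T0, always adjusting gives 58% at r = 0.5 and 75% at r = 0.7, against about 48% under the rule. This plan's contrasts already use T0, and no prognostic correlation is given. Power is at most forgone; none is lost against no adjustment.
- **That the estimand changes with every chance finding.** In a linear model, adjusting for a pre-randomisation covariate leaves the mean-difference estimand unchanged. Only T1 adjustment could alter what is estimated.
- **That false positives increase.** The simulated rule is slightly conservative.
- **That T1-T0 is always pulled toward zero.** Mean bias needs a post-allocation shift.

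**Conclusion.** The point holds. As a check of randomisation, the T1 comparison is invalid by the article's own timeline. As a source of covariates, it conflicts with T1's place among the responses. Neither conclusion depends on an assumed number.

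The size does. A false flag somewhere among the T1 scores has a chance of up to about one half (independence and a .05 level assumed). A reduction of T1-T0 from 0.40 to about 0.26 needs a 0.4 SD shift, correlation 0.5 and a covariate that acts on the contrast. Under such a shift a T0-adjusted T2 effect can also be attenuated. Without a shift there is no mean bias.

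For baseline variables, the rule selects by chance and gains almost nothing over no adjustment. The precision forgone is probably small where T0 is already in the contrasts. It could be larger for a T0-adjusted analysis with a strongly prognostic covariate. This is a correction that should be made, not a defect that invalidates the trial.

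**What to change.** - Delete the sentence that makes adjustment depend on significant differences.
- Name in advance, for every model and regardless of significance, covariates measured at or before T0: T0 MMSE, and the randomisation factors gender and nursing home. Handle the outcome's T0 value in the model itself.
- Report T0 characteristics and scores by arm descriptively, without tests, and stop describing a T1 comparison as a check of randomisation.
- Keep T1 as an outcome only, and never use it as a covariate in a model in which T1 is a response.

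The cost is wording, because these data are already collected or known at T0. The models lose a few degrees of freedom: one for MMSE, one for gender and three or four for four or five homes, so five or six in all.

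In return, the adjustment set no longer depends on chance, and T1-T0 stays readable as the change before treatment.
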